#### Imprint Assessment With Paired Recognition (Visual Paired Comparison by Neurotrack)

A tablet-integrated camera was used to record a video of the participant’s face while they were seated comfortably in a quiet, well-lit room in front of a tablet computer. Participants were shown a series of paired images during a familiarization phase and were then exposed to novel images. A second learning and test phase assessed paired associate learning and memory. Trial-level multimodal cognitive data (saccades, oscillations, gaze duration, and blinks), keystroke latency, performance accuracy, and discriminability for every participant on their digital multimodal cognitive tasks were collected. From these measures, measures of visual episodic memory, visual working memory, processing speed, executive function, and recognition discriminability will be derived.

### Participant Feedback Survey

A brief participant feedback survey was adapted from the Subject Usability Scale [43] and National Aeronautics and Space Administration Task Load Index [44] and was used in the MEDIA study to evaluate the participants’ experience and acceptance of the digital tools and assessments. The survey included 7 statements: “The device was easy to use”; “I needed to learn many things before I could get going with this device”; “This assessment was mentally demanding”; “This assessment was physically demanding”; “I enjoyed this assessment”; “I was insecure and/or frustrated during this assessment”; and “This assessment felt meaningful and relevant to difficulties I have in my daily life.” For these statements, participants indicated their degree of agreement or disagreement on a 6-point Likert scale ranging from 0 (strongly disagree) to 5 (strongly agree). There was an open question—“Is there anything else you would like to add?”—for open comments from the participants on the assessments.

### Statistical Analysis

As this is an exploratory study, the sample size was chosen pragmatically to balance statistical and feasibility considerations. Data from 12 participants per cohort were considered to provide sufficient information for the study objectives [45].

Descriptive statistics (ie, mean, median, range, and SD) of the total score from each conventional end point and questionnaire will be reported by the cohort. Estimates of the between-cohort standardized differences in the corresponding total scores will be provided.

Digital technologies will produce ≥1 outcome variable (features) for each participant and assessment time. On the basis of these features, psychometric properties will be assessed: acceptable range (ceiling and floor effects), reliability (test-retest variability), validity (correlation to conventional end points), and responsiveness (change from test and retest to challenge) as appropriate. Various statistical rules for classifying participants into cohorts will be explored. The goodness of these rules will be assessed by calculating the sensitivity, specificity, positive predictive value, and negative predictive value. Receiver operating characteristics curves will be constructed to determine cutoff points with the best trade-off between sensitivity and specificity. Data from the participant feedback survey will be summarized descriptively.

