### Participants

The study was conducted at an academic Memory Clinic in the Geriatric Department of Landspítali University Hospital in Reykjavik, Iceland. Participants were grouped into 4 cohorts derived from 2 sources. The 2 cohorts comprised cognitively healthy amyloid-negative (controls; cohort 1) and cognitively healthy amyloid-positive (presymptomatic; cohort 2) male and female participants. These participants had been investigated using either cerebrospinal fluid (CSF) analysis or amyloid positron emission tomography (PET) up to 2 years earlier. The other 2 cohorts comprised male and female individuals who had been referred to the Memory Clinic by their primary health care physician and had either been diagnosed with mild cognitive impairment (MCI; predementia; cohort 3) or mild AD (mild dementia; cohort 4) at the Memory Clinic. The participants were aged between 60 and 80 years. The clinical diagnosis of MCI and mild AD was made according to the National Institute on Aging and Alzheimer Association criteria [14]. A total of 53 participants were enrolled in the study, of whom 3 (6%) failed the screening criteria (because of the Mini-Mental State Examination score being <20), resulting in a total of 50 (94%) participants who were included in the study: 13 (26%) were controls, 12 (24%) were presymptomatic, 13 (26%) were predementia, and 12 (24%) had mild dementia. Of the 50 participants, 4 (8%) discontinued the study after finalizing visit 2; hence, 46 (92%) participants completed all study visits: 12 (26%) were controls, 12 (26%) were presymptomatic, 11 (24%) were predementia, and 11 (24%) had mild dementia. The data of all 50 participants were used for further analysis where applicable; that is, for all analyses performed on the data up to visit 3. The detailed inclusion and exclusion criteria are listed in Multimedia Appendix 1, and protocol deviations are listed in Multimedia Appendix 2.

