### Conclusions

Although the surge of novel technologies is revolutionizing the way we approach cognitive testing, the challenge of systematically evaluating the performance of these digital end points remains. The MEDIA study delivers technology feasibility evaluations of 10 novel in-clinic digital end points and determines whether these tools provide tolerable and reliable measures of cognition, with improved psychometric properties and greater sensitivity and specificity than conventional clinical trial assessments. The MEDIA study psychometrically evaluates multiple digital cognitive end points head to head with conventional end points, as well as in a mild cognitive challenge model. Digital end point methodology studies such as the MEDIA study can efficiently avoid costly failures of improper digital end point implementation in clinical drug trials. Moreover, the MEDIA study may identify more sensitive screening tools for the earlier detection of AD, as well as potentially superior efficacy readouts for use in clinical drug development. A noninterventional study such as this is an important step toward establishing reliable and valid digital technologies ready to be used as efficacy end points in future clinical drug trials.

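### In-sample PPV and NPV will reflect the near-equal cohort sizes set by design, so they estimate no population's predictive value and cannot be compared between contrasts

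*Protocol article*

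**What the plan says.** The Statistical Analysis section of the protocol article says that various rules for assigning participants to cohorts will be explored. It then names four measures of how good they are: "The goodness of these rules will be assessed by calculating the sensitivity, specificity, positive predictive value, and negative predictive value". It gives no prevalence at which PPV and NPV apply.

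On sample size, the same section says that "the sample size was chosen pragmatically to balance statistical and feasibility considerations" and that "Data from 12 participants per cohort were considered to provide sufficient information for the study objectives".

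The Participants section states that "Participants were grouped into 4 cohorts derived from 2 sources". The two cognitively healthy cohorts had earlier amyloid results: "These participants had been investigated using either cerebrospinal fluid (CSF) analysis or amyloid positron emission tomography (PET) up to 2 years earlier". The other two were referrals to the memory clinic with a diagnosis of mild cognitive impairment or mild AD. The included numbers were "13 (26%) were controls, 12 (24%) were presymptomatic, 13 (26%) were predementia, and 12 (24%) had mild dementia"; those who completed all visits were "12 (26%) were controls, 12 (26%) were presymptomatic, 11 (24%) were predementia, and 11 (24%) had mild dementia".

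The Conclusions section adds that "the MEDIA study may identify more sensitive screening tools for the earlier detection of AD". The Limitations section covers sample size, the challenge model, the single site, sex, education and historical amyloid status. It does not mention the fixed cohort mix.

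**The concern.** Sensitivity and specificity condition on the true cohort, so for a given pair of cohorts they do not depend on how many of each were recruited. PPV and NPV condition on the test result and mix accuracy with the share of positives. When each group is filled to a target number from its own source, that share is a design constant and not a prevalence. The in-sample PPV then does not estimate the chance that a person who tests positive in any real setting belongs to the target group.

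Two things are at stake. First, the article lists PPV and NPV as measures of goodness, yet they move when accuracy does not. The contrasts are not fixed, so the same rule can look mediocre or excellent according to which cohorts are pooled as positive. Second, the article mentions possible screening use, where a reader may well take PPV at face value, and nothing in the text confines it to the study mix.

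**Working it through.** **Inputs from the article.** Included participants by cohort: 13, 12, 13, 12, total 50. Shares: 13/50 = 0.26 and 12/50 = 0.24, which match the printed percentages. Completers: 12, 12, 11, 11 of 46, or 0.26, 0.26, 0.24, 0.24, which also match. The article gives no PPV, NPV or external prevalence, so there is no such figure to reproduce.

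**Assumptions.** Sensitivity (Se) and specificity (Sp) both 0.80, with 0.70 and 0.90 as a range. Outside prevalences of 10%, 20% and 70%, chosen to span low to high. None of these is in the article.

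**Formulas.** With p the share of positives:

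- PPV = Se·p / [Se·p + (1 − Sp)(1 − p)]
- NPV = Sp(1 − p) / [Sp(1 − p) + (1 − Se)p]
- LR+ = Se / (1 − Sp); LR− = (1 − Se) / Sp

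**PPV at the study mix, Se = Sp = 0.80.**

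- One cohort against the rest, p = 12/50 = 0.24: 0.192 / (0.192 + 0.152) = 0.558
- One cohort against the rest, p = 13/50 = 0.26: 0.208 / (0.208 + 0.148) = 0.584
- Pairwise, p = 12/25 = 0.48: 0.384 / (0.384 + 0.104) = 0.787
- Pairwise, p = 13/25 = 0.52: 0.416 / (0.416 + 0.096) = 0.8125
- Cohorts 2-4 against controls, p = 37/50 = 0.74: 0.592 / (0.592 + 0.052) = 0.919

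NPV moves the other way: 0.608 / (0.608 + 0.048) = 0.927 at p = 0.24, and 0.208 / (0.208 + 0.148) = 0.584 at p = 0.74. The likelihood ratios stay the same throughout: LR+ = 0.80/0.20 = 4 and LR− = 0.20/0.80 = 0.25.

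**The same rule at assumed outside prevalences.**

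- 10%: 0.08 / (0.08 + 0.18) = 0.308
- 20%: 0.16 / (0.16 + 0.16) = 0.500
- 70%: 0.56 / (0.56 + 0.06) = 0.903

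**PPV over a range of accuracy.**

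| Se = Sp | p = 0.24 | p = 0.48 | p = 0.74 | 10% | 20% | 70% |
|---|---|---|---|---|---|---|
| 0.70 | 0.424 | 0.683 | 0.869 | 0.206 | 0.368 | 0.845 |
| 0.80 | 0.558 | 0.787 | 0.919 | 0.308 | 0.500 | 0.903 |
| 0.90 | 0.740 | 0.893 | 0.962 | 0.500 | 0.692 | 0.955 |

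**A rule with no information.** With Se = Sp = 0.50, PPV = p exactly: 0.24, 0.48 or 0.74. A useless rule therefore scores a PPV of 0.74 in the contrast of cohorts 2-4 with controls.

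**Pooled contrasts.** Write s1 to s4 for the cohort-specific proportions classified correctly under the contrast in question. For mild dementia against the rest, Sp = (13·s1 + 12·s2 + 13·s3)/38, so predementia carries weight 13/38 = 0.34 because of recruitment. For cohorts 2-4 against controls, Se = (12·s2 + 13·s3 + 12·s4)/37. The cohort mix thus enters sensitivity or specificity wherever cohorts are pooled. It does not do so in pairwise contrasts.

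**The case against.** The best case for the plan has several parts.

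- **No stated decision rests on PPV or NPV.** The Statistical Analysis section chooses cutoffs on the trade-off between sensitivity and specificity. The Conclusions frame the comparison with conventional tests in those two terms as well. Advancement depends on a separate scoring system that is not shown. This stands, and it limits the harm.
- **The method of calculation is not spelled out.** The article does not say that PPV and NPV will be taken at the raw sample mix, and an analysis plan could standardise or label them. This stands in part. The point concerns what the article does state: two prevalence-dependent quantities, named without qualification as measures of goodness in a sample with a fixed mix.
- **The study is exploratory and calls for confirmation in larger trials.** That covers imprecision. A larger sample with the same fixed mix would give the same wrong target.

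Three stronger readings are tempting, and the article does not support them.

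- A reader might infer that predictive values cannot be compared between technologies. For a given contrast and the same participants the share of positives is the same, so ranking remains possible; it weakens only where missing data change who is analysed.
- A reader might infer that in-sample PPVs always flatter, or that 0.31 is the true value. That figure belongs to an assumed 10% prevalence. At an assumed 70% the PPV is 0.90, above the one-against-rest and pairwise values, so the gap can run either way.
- A reader might infer that the predictive values are meant for selecting participants for drug trials. The stated purpose is efficacy end points, and screening appears once as a hedged remark.

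**Conclusion.** The point holds as a correction to how two of the four named measures are used. Taken from this sample, PPV and NPV reflect the design mix, estimate no population's predictive value, and cannot be compared between contrasts. At an assumed sensitivity and specificity of 0.80, the choice of contrast alone moves PPV from 0.56 to 0.92. That the values depend on the mix follows from the recruitment design and needs no assumption. The sizes do rest on the assumed accuracy and, for the outside comparison, on assumed prevalences.

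Sensitivity and specificity for a pair of cohorts are not affected by the cohort ratio, nor are the corresponding ROC curves. A reader might infer that Bayes' rule at a single prevalence would cure everything. It would not for pooled contrasts, because their sensitivity or specificity already carries the recruitment mix.

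**What to change.** The analyses are written in the future tense, so the change can still be made.

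- Judge the classification rules on sensitivity, specificity and likelihood ratios, each with an interval, preferably for pairwise contrasts. Where cohorts are pooled, say that the figures depend on the study's cohort proportions.
- If predictive values are wanted, compute them by Bayes' rule from those estimates over a stated range of prevalences, from a low screening value to a high memory-clinic value.
- Failing that, keep the in-sample PPV and NPV but label them as specific to the study mix and not for screening use, and add the fixed mix to the limitations.

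The cost is a sentence or two and a small amount of extra analysis, with no change to data or recruitment. The downside is that some PPVs may look less favourable.

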#### Digital Clock-Drawing and Cognitive Tablet-Based Drawing Tests (DCTclock by Linus Health)

##### DCTclock

DCTclock [41,42] is a digitized version of the standard rapid and noninvasive pen-and-paper neuropsychological clock-drawing test. The test involves participants drawing 2 clock faces on a piece of paper with a digital pen that precisely tracks and records the drawing behavior. The time-stamped positional data (x and y coordinates and time stamps) generated during this assessment are analyzed using proprietary machine learning algorithms that evaluate hundreds of features captured by the drawing process and the final output. By comparing test results with normative data, the system then determines whether the test is within normal limits and provides a detailed breakdown of performance on the various cognitive tasks evaluated during the test.

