## Discussion

### Expected Findings

The expected main findings of this study are as follows: (1) the accuracy of each of the 10 technologies in classifying participants into 4 cohorts according to the severity of cognitive impairment and dementia; (2) the psychometric properties of each of the digital technologies tested, including acceptable range (ceiling and floor effects), concurrent validity (correlation of ≥1 outcome measure of each of the technologies to traditional paper-and-pencil tests in AD), reliability (concordance of test and retest), and responsiveness (the sensitivity to change in a mild cognitive challenge model); and (3) feasibility of applying these technologies in drug trials based on study participant feedback.

Digital technologies hold promise in amending psychometric limitations associated with many conventional paper-and-pencil end points and transforming the way drug treatment effects are measured in clinical trials. For example, the digital pen used in this study to augment standard cognitive tests may reduce subjectivity and variability of well-established paper-and-pencil tests such as the clock-drawing test, trail-making test, or digit-symbol substitution test [42]; computerized testing implemented on tablets or smartphones with short cognitive test batteries may allow more frequent monitoring of cognition in the real world, thereby reducing variability and bias [47-49]; eye tracking while reading and voice analytics of conventional picture description tests may provide direct physiological assessments of cognition, which may increase sensitivity [30-37]; and AR or virtual reality testing may introduce more real-life assessments in a clinical setting [50,51]. More accurate and reliable efficacy end points could potentially reduce the number of failed or inconclusive trials and allow for more efficient drug development through shorter, smaller, less costly, and less burdensome drug trials, ultimately allowing more drugs to be studied and medicines to reach patients faster. However, it remains unclear how to best evaluate a wide range of novel and promising technologies, how to use them to derive efficacy end points, and how to advance them through early drug development processes.

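### As described, classification rules and ROC cutoffs are chosen and graded on the same 50 participants, so reported accuracy will be optimistic, most of all for feature-rich technologies

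*Protocol article*

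**What the plan says.** The Statistical Analysis section sets out the classification work in three steps. First, "Various statistical rules for classifying participants into cohorts will be explored". Second, the rules are judged by sensitivity, specificity, positive predictive value and negative predictive value. Third, "Receiver operating characteristics curves will be constructed to determine cutoff points with the best trade-off between sensitivity and specificity". It says that each technology yields at least one feature per participant and assessment time, and gives no total.

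The Participants section gives the data available: "13 (26%) were controls, 12 (24%) were presymptomatic, 13 (26%) were predementia, and 12 (24%) had mild dementia". On the number of participants, the Statistical Analysis section says "As this is an exploratory study, the sample size was chosen pragmatically to balance statistical and feasibility considerations" and "Data from 12 participants per cohort were considered to provide sufficient information for the study objectives". No accuracy target, precision target, alpha or power accompanies it.

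The first expected main finding, under Expected Findings, is "the accuracy of each of the 10 technologies in classifying participants into 4 cohorts". The Conclusions section adds that the study determines whether the tools have better sensitivity and specificity than conventional assessments. The article mentions no hold-out sample, cross-validation, bootstrap correction or externally fixed cutoff.

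**The concern.** A cutoff taken from a ROC curve at the point that looks best in a sample fits the chance pattern of that sample. Scoring it on the same people returns that chance pattern as accuracy. Choosing among rules and among features adds to the effect. With 12 or 13 people per cohort, chance patterns are large.

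Two results are exposed. One is the absolute accuracy of each technology, which is the first expected main finding. The other is the comparison with conventional tests. A paper-and-pencil total score is one number with a known direction, whereas a digital tool may offer many features from which the best is kept. The tool with more candidates therefore gains an advantage unrelated to its merit. This matters most for controls against presymptomatic participants: Table 1 shows mean MMSE of 29.5 and 29.7 and mean RBANS of 101 and 98.4, so conventional tests show little separation and an inflated digital result would stand out.

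**Working it through.** **The plan's own figures.** The cohort sizes add up: 13 + 12 + 13 + 12 = 50, against a planned 4 × 12 = 48. The 12 per cohort cannot be re-derived because no error rate, effect size or precision is stated. The article gives no accuracy figure to reproduce.

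**Inputs from the article.** Cohort sizes 13, 12, 13 and 12; cutoff chosen at the best trade-off on the ROC curve; several rules explored.

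**Assumptions not in the article.** The number of candidate features k is varied from 1 to 20. Features are independent normal noise, and the direction of effect is free unless stated. The best trade-off is taken as the largest Youden index.

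**Formulas.** J = sensitivity + specificity − 1. Balanced accuracy = (sensitivity + specificity)/2 = (1 + J)/2. For noise the true J is 0 and the true balanced accuracy is 0.50.

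**Step 1: two-group contrasts.** In each simulated data set the largest J over all cutoffs was found for each feature, and the best of k features was kept. Means over simulations:

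| k | 13 vs 12: J | balanced accuracy | chance of ≥0.75 | 25 vs 25: J | balanced accuracy | chance of ≥0.75 |
|---|---|---|---|---|---|---|
| 1 | 0.315 | 0.658 | 7% | 0.227 | 0.614 | 0.2% |
| 5 | 0.442 | 0.721 | 30% | 0.318 | 0.659 | 0.9% |
| 10 | 0.492 | 0.746 | 51% | 0.355 | 0.677 | 2% |
| 20 | 0.539 | 0.769 | 76% | 0.388 | 0.694 | 4% |

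For example, at 13 vs 12 with k = 10: (1 + 0.492)/2 = 0.746. The 25 vs 25 columns pool cohorts 1 and 2 against cohorts 3 and 4.

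**Step 2: cutoff choice alone.** One noise feature with its direction fixed in advance gives mean J = 0.217 at 13 vs 12, so balanced accuracy is (1 + 0.217)/2 ≈ 0.61. This is the position of a conventional total score that carries no information. Against the best of 20 features, the head start from the search is 0.77 − 0.61 = 0.16.

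**Step 3: four-cohort rule.** A linear discriminant rule on p noise features, with cohorts of 13, 12, 13 and 12, was scored on its own 50 people and on 50 new people:

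| p | own sample | new people |
|---|---|---|
| 1 | 31% | 25% |
| 5 | 44% | 25% |
| 10 | 55% | 26% |
| 20 | 75% | 25% |

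**Step 4: precision.** Even an unbiased sensitivity of 10/12 has a Clopper-Pearson 95% interval of 0.52 to 0.98.

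**The case against.** The strongest reply is that the article is silent on internal validation and does not exclude it. An article condenses, and a full protocol or analysis plan may hold a correction. That stands as a limit: the inflation applies to the analysis as described here. But the article does state a procedure, namely choosing the best cutoff and grading the rules, and that procedure is biased unless something is added.

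A second reply is that the study is exploratory and the Limitations section asks for confirmation in larger trials. That caveat is tied to small sample size, which readers take to mean imprecision. It does not say that the estimates lean upward, and the Conclusions section still makes a comparative claim.

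Three stronger readings are tempting, and the documents do not support them:

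- A reader might infer that hundreds of features are searched on these 50 people. The DCTclock section does mention "proprietary machine learning algorithms that evaluate hundreds of features captured by the drawing process", but these feed a vendor algorithm whose results are compared with normative data. They are not listed as separate candidate predictors.
- A reader might infer that validity is met once a single measure correlates. Expected Findings speaks of "correlation of ≥1 outcome measure of each of the technologies to traditional paper-and-pencil tests in AD", which describes what will be correlated and sets no pass rule.
- A reader might infer that accuracy ranking alone decides which tools advance. The Background describes predefined success criteria from a scoring system, within a step that also covers feasibility and patient acceptance.

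It also stands that some technologies already have a lead outcome, that related features (several gait parameters, for instance) lower the effective k, and that the pooled contrast is much milder.

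**Conclusion.** The point holds for the procedure as the article describes it: sensitivity, specificity and both predictive values will be optimistic, and the comparison with conventional tests leans toward technologies with more candidate features.

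The size depends on a feature count that the article does not give. Over 1 to 20 independent noise features with free direction, the inflation of balanced accuracy is 0.16 to 0.27 for 13 vs 12 (0.66 − 0.50 and 0.77 − 0.50) and 0.11 to 0.19 for 25 vs 25 (0.61 − 0.50 and 0.69 − 0.50). For a 10-feature four-cohort rule it is about 30 percentage points (55% − 25%). Correlation among features would shrink these figures, as would use of a single vendor score built on other data.

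That noise could pass for a useful test is well supported for single-cohort contrasts and for multi-feature four-cohort rules. It is weakly supported for the pooled contrast, where reaching 0.75 has a chance of only 2% at 10 features.

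**What to change.** - Make optimism-corrected accuracy the headline result for every technology, by cross-validation or bootstrap, with feature selection, rule choice and cutoff choice all repeated inside each resample.
- Report intervals with each figure.
- Put the conventional tests through the same procedure, so that the comparison in the Conclusions section is like with like.
- Keep in-sample figures if wanted, labelled as apparent.
- Where a composite or key outcome already exists, use it as the lead feature. Examples are the Digital Neuro Signature score and the key outcome measures named for the computerized cognitive tests.

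If the full protocol or analysis plan already does this, one sentence in the Statistical Analysis section settles the point.

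The cost is additional programming and wording, with no new data. The reported accuracies will be lower and their intervals wider.
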